**4.2 Randomisation** 
The due date is based on biometrics determined by nuchal translucency scan (at 12 weeks) with duration of pregnancy of 280 days. 
Randomisation is performed with an automatic computerized telephone system (Voice response) that meets international requirements. The randomisation is stratified by centre and previous caesarean section. 
According to the randomisation protocol, the obstetrician schedules the date of surgery in collaboration with the staff booking the ECS. The procedure is booked according to a prioritized gestational age sequence:

| EARLY ECS (38+3)   1. 38+3 2. 38+2 3. 38+4 4. 38+5 5. 38+1 | LATE ECS (39+3)   1. 39+3 2. 39+4 3. 39+2 4. 39+1 5. 39+5 |
| --- | --- |

**4.3 Blinding** 
The trial cannot be performed as a blinded study. 
The staff is instructed not to express any personal preferences in their interaction with the pregnant women. Open data analyses are carried out.

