**4.1 Outcomes**

Primary outcome:

- Neonatal morbidity causing admission to neonatal ward within the first 2 days of life

Secondary outcomes:

1. Admission to neonatal unit within 7 days after birth
2. Neonatal length of stay and ICD-10 diagnoses for hospitalized children
3. Neonatal treatment and duration of treatment: Mechanical ventilation, CPAP, oxygen supplementation, intravenous antibiotics
4. Outpatient treatment or control, or admission to a neonatal unit or paediatric ward within 2 months or 2 years after birth
   1. Department or physician, date of admission and discharge, ICD-10 codes, treatment, type of medical treatment.
5. Maternal morbidity within 30 days
   1. Perioperative complications: Uterine incision lateral tear, blood loss, laceration of bladder or intestine, other intraoperative complications
   2. Postoperative complications: Blood transfusion, need of re-operation, antibiotic treatment, and total hospital stay.
6. Logistics
   1. Acute caesarean section (8 hours from decision to execution)
   2. Reason for acute caesarean section: labour, PROM, foetal indication, pregnancy complications, maternal request
   3. Time of delivery
   4. Education & training of operating physicians
7. Child’s nutritional status after 2 months
8. Mother’s preference for time of caesarean at any subsequent pregnancy.

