**4.4 Data collection**
Data are retrieved from the individual patient records and are entered into a study data registration form. 
Data regarding the child's progress within 2 months and 2 years after birth are retrieved either from medical records on the data registration form or are extracted from the Danish National Board of Health's national patient Register using the relevant personal security numbers (CPR). 
Data from the registration form are entered into EpiData by a secretary at the Perinatal Research Unit. Data from the questionnaire are downloaded from the server (Ramboll, SurveyXact). 
Data are kept confidential and in accordance with Danish Law. Obstetricians in charge of the study at each facility and project staff are responsible for correct data handling and storage. The project has been approved by the Danish Data Protection Agency.

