**5. Power calculation**
The sample size is calculated on the basis of the primary endpoint of neonatal ward admission within the two days after birth, using data from an existing birth cohort from the same population. Approx. 14% of those delivered by early caesarean section and 8% of those delivered by late caesarean section are hospitalized. With a significance level of 5% and a power of 0.80, the calculated sample size is 459 in each group. With non-compliance of around 9%, the total number of enrolled participants is calculated to approx. 1,270 women.

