**6. Project location and participants** 
Participants are recruited from Aarhus University Hospital Skejby, Hospital of Aalborg, Regional Hospitals of Herning, Viborg, and Randers, Kolding Hospital, and Odense University Hospital. The inclusion is initiated March 2009. 
An obstetrician at each hospital unit serves as local project manager (at Skejby the principal investigator). Each trial unit is compensated in the amount of DKK 700 for each participating woman, which corresponds to the time spent on inclusion, data collection, etc. All involved staff groups receive instruction as to the project’s background and practical aspects. 
The group of physicians perform caesarean section according to the joint Danish O&G professional guidelines (DSOG). All women receive prophylactic antibiotics intraoperative as well as thrombosis treatment (if indicated) after birth. A paediatrician is not routinely present at the ECS.

Around 2,235 children are delivered by caesarean section annually at the seven participating hospitals (2007). It is considered feasible to include 600 pregnant women annually. The inclusion period runs from 1 March 2009 and until the sample size is reached. From January 2011, the study only includes women with a due date earlier than 30 August 2011. This is expected to yield a total of approx. 1,300 included women (due to the restrictions on the due date in 2011). 
The study as a whole may be discontinued if it fails to recruit enough participants. As data are analysed in an open fashion and there are no plans for any interim analysis, we will not obtain information about significant differences in morbidity between the two groups that could cause the study to be terminated before it stops.

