**7. Data processing and analyses** 
Data collected from the two groups are used in a comparative analysis to identify any inter-group differences on the specified parameters. 
Statistical variables will be calculated according to the intention-to-treat principle and per-protocol using the analytical software program STATA. The primary endpoint will be analysed with a 5% significance level. The budget foresees the need for a statistician to assist with the data analyses.

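### The protocol prescribes an open data analysis although only the surgery is unblindable, and it provides no masked classification of a primary outcome that one section defines by the cause of admission

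*Protocol*

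**What the plan says.** Protocol section 4.3 (Blinding) states "The trial cannot be performed as a blinded study", asks staff not to voice preferences to the women, and then adds "Open data analyses are carried out". Section 6 (Project location and participants) repeats the open status in passing: "As data are analysed in an open fashion and there are no plans for any interim analysis". Neither place gives a separate reason for leaving the analysis unmasked.

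The primary outcome is worded in two ways:
- Section 4.1 (Outcomes): "Neonatal morbidity causing admission to neonatal ward within the first 2 days of life"
- Section 5 (Power calculation): "primary endpoint of neonatal ward admission within the two days after birth"

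On how outcomes reach the database, section 4.4 (Data collection) says "Data are retrieved from the individual patient records and are entered into a study data registration form" and "Data from the registration form are entered into EpiData by a secretary at the Perinatal Research Unit". It does not say whether the person abstracting or classifying an admission knows the arm. On analysis, section 7 plans intention-to-treat and per-protocol results with the primary endpoint at the 5% level, and says "The budget foresees the need for a statistician to assist with the data analyses".

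**The concern.** The woman, the surgeon and the ward staff cannot be masked to the week of delivery. That does not carry over to someone running a comparison of two coded groups, and it carries over only in part to someone deciding from a file whether morbidity caused an admission. The protocol nevertheless commits itself to an open analysis.

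This matters more here than for a bare count of admissions. Under the section 4.1 wording, an admitted infant is an event only if morbidity was the cause. Borderline admissions then need a decision. Choosing between the section 4.1 and section 5 wordings after seeing results by arm would itself be an arm-aware decision. Such decisions also have a direction in which to lean: section 8.1 expects more respiratory complications with early surgery, and section 5 plans on 14% against 8%.

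At stake is a small but avoidable source of bias in the final classification and the primary comparison. This is a different matter from whether anyone sees interim results.

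**Working it through.** **1. Inputs.** From section 5: 14% early, 8% late, 5% significance level, power 0.80, 459 per group, 9% non-compliance, about 1,270 in total (635 per arm). The protocol does not state sidedness; two-sided is assumed because it reproduces the figure.

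**2. The plan's own figures.** Pooled rate p̄ = (0.14 + 0.08)/2 = 0.11.

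n = [1.960·√(2·0.11·0.89) + 0.842·√(0.14·0.86 + 0.08·0.92)]² / 0.06² = 425.7, so 426 per group.

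With continuity correction: n' = (n/4)·[1 + √(1 + 4/(n·0.06))]² = 458.4, so 459. This matches the protocol.

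For the total, 9% crossover in each arm gives 0.14·0.91 + 0.08·0.09 = 13.46% and 0.08·0.91 + 0.14·0.09 = 8.54%. The uncorrected formula then gives 634 per arm, or 1,268, in line with about 1,270. Masking changes none of these inputs, so the sample size is not affected.

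**3. Number of admissions.** 635 × 0.14 = 88.9 and 635 × 0.08 = 50.8, about 89 and 51, or about 140 in total. This ignores crossover.

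**4. Effect of a net shift between arms.** Suppose there is no true difference, and arm-aware classification leaves rates p and p + s. With n = 635 and p̄ = p + s/2:
- SE₀ = √(2p̄(1 − p̄)/n)
- SE₁ = √{[p(1 − p) + (p + s)(1 − p − s)]/n}
- rejection probability = Φ[(s − 1.960·SE₀)/SE₁] + Φ[(−s − 1.960·SE₀)/SE₁]

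For p = 0.08 and s = 0.01: SE₀ = 0.01565, SE₁ = 0.01565, giving 0.0932 + 0.0047 = 0.098.

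| Net shift | Infants at 635 per arm | False-positive rate, base 8% | Base 11% |
|---|---|---|---|
| 0 | 0 | 5.0% | 5.0% |
| 0.5 point | 3.2 | 6.2% | 5.9% |
| 1 point | 6.35 | 9.8% | 8.6% |
| 2 points | 12.7 | 23.8% | 19.5% |

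**5. How much doubt such a shift needs.** The documents give no share of admissions with a debatable cause, so the share d is an assumption. In the most extreme case every debatable admission counts in one arm and none counts in the other. With a common admission rate A, the classified rates are then A and A(1 − d), a gap of A·d.
- 9% against 8% needs d = 1/9, about 11%.
- 8.5% against 8% needs d = 0.5/8.5, about 6%.
- At A = 8%, d of 5%, 10% or 20% caps the gap at 0.4, 0.8 or 1.6 points.

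A full point therefore requires more than a tenth of admissions to be debatable and every one to be settled in the same arm's direction. Real shifts should be smaller.

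**6. The two endpoint wordings side by side.** Under section 5, the event is a dated admission within two days, and little remains to classify. Under section 4.1, cause must be settled for each admission. The value of masked classification depends almost entirely on which wording governs. The value of a masked analysis does not, though for a binary endpoint analysed by intention to treat it is limited.

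**The case against.** The strongest defence has four parts.

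- **The main route for bias is untouched.** Whether an infant is admitted is decided at the bedside, where gestational age is normally known. Neither a stripped extract nor A/B labels change who was admitted. This stands, and it is why the expected gain is modest.
- **The analysis leaves little discretion.** A recorded binary event, compared by intention to treat at a fixed level, gives an analyst few choices. This stands if section 5 defines the event, and only in part if section 4.1 does.
- **Masking is imperfect and not free.** The arms are defined by gestational age, so source records largely reveal the arm, and staff who abstracted a record have already seen it. An extract must be prepared and the code opened later. This stands: the cost is low, not nil.
- **Procedures for coding may sit elsewhere.** Abstraction rules are often left to an analysis plan or data manual. This stands for coding. It does not answer the open-analysis statement, which the protocol itself makes twice.

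A reader might infer more than the text supports. The protocol does not declare outcome coding open: section 4.3 speaks of analyses, and section 4.4 is silent. The ICD-10 diagnoses belong to a secondary outcome, not to the primary event. The statistician sentence in section 7 concerns the budget and does not say who runs the primary comparison. Nothing in the document shows that any admission would be misclassified.

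**Conclusion.** The point holds in a limited form. The protocol fixes an open analysis without a reason that applies to the analyst, and it describes no masked classification for an outcome that section 4.1 ties to cause. A better method is available at low cost. This is a worthwhile improvement, not a contradiction in the blinding section or a demonstrated bias.

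The size is illustrative: a false-positive rate of about 6% for a half-point net shift and about 10% for a full point, against a nominal 5%. Both figures assume no true difference, 635 per arm, an 8% base rate and a two-sided test. The full-point case also needs at least about 11% of admissions to be debatable and all to be resolved in one direction, which is an extreme assumption. If plain admission is confirmed as the endpoint, the classification part largely falls away and only the masked comparison remains.

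**What to change.** 1. Before analysis, reconcile the endpoint wording in sections 4.1 and 5, so that it is settled whether cause of admission is part of the primary event.
2. If cause is kept, classify each admission from an extract holding diagnosis, treatment and time from birth to admission, without arm, calendar dates or gestational age. Where possible, use project staff who did not abstract that record.
3. Replace the open-analysis sentence in section 4.3, and align sections 6 and 7: the intention-to-treat primary comparison is programmed and finalised with arms coded A and B, and the code is opened only afterwards.
4. Build the per-protocol set separately after unmasking, since timing of delivery reveals the arm.

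The cost is a few sentences of text, preparation of the stripped extract and a slight delay before unmasking. Sample size and trial procedures do not change. Bias in the bedside admission decision remains and should be acknowledged as a limitation of the open-label design.

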**4.4 Data collection**
Data are retrieved from the individual patient records and are entered into a study data registration form. 
Data regarding the child's progress within 2 months and 2 years after birth are retrieved either from medical records on the data registration form or are extracted from the Danish National Board of Health's national patient Register using the relevant personal security numbers (CPR). 
Data from the registration form are entered into EpiData by a secretary at the Perinatal Research Unit. Data from the questionnaire are downloaded from the server (Ramboll, SurveyXact). 
Data are kept confidential and in accordance with Danish Law. Obstetricians in charge of the study at each facility and project staff are responsible for correct data handling and storage. The project has been approved by the Danish Data Protection Agency.

**5. Power calculation**
The sample size is calculated on the basis of the primary endpoint of neonatal ward admission within the two days after birth, using data from an existing birth cohort from the same population. Approx. 14% of those delivered by early caesarean section and 8% of those delivered by late caesarean section are hospitalized. With a significance level of 5% and a power of 0.80, the calculated sample size is 459 in each group. With non-compliance of around 9%, the total number of enrolled participants is calculated to approx. 1,270 women.

**6. Project location and participants** 
Participants are recruited from Aarhus University Hospital Skejby, Hospital of Aalborg, Regional Hospitals of Herning, Viborg, and Randers, Kolding Hospital, and Odense University Hospital. The inclusion is initiated March 2009. 
An obstetrician at each hospital unit serves as local project manager (at Skejby the principal investigator). Each trial unit is compensated in the amount of DKK 700 for each participating woman, which corresponds to the time spent on inclusion, data collection, etc. All involved staff groups receive instruction as to the project’s background and practical aspects. 
The group of physicians perform caesarean section according to the joint Danish O&G professional guidelines (DSOG). All women receive prophylactic antibiotics intraoperative as well as thrombosis treatment (if indicated) after birth. A paediatrician is not routinely present at the ECS.

Around 2,235 children are delivered by caesarean section annually at the seven participating hospitals (2007). It is considered feasible to include 600 pregnant women annually. The inclusion period runs from 1 March 2009 and until the sample size is reached. From January 2011, the study only includes women with a due date earlier than 30 August 2011. This is expected to yield a total of approx. 1,300 included women (due to the restrictions on the due date in 2011). 
The study as a whole may be discontinued if it fails to recruit enough participants. As data are analysed in an open fashion and there are no plans for any interim analysis, we will not obtain information about significant differences in morbidity between the two groups that could cause the study to be terminated before it stops.

**Inclusion criteria**
• Scheduled for ECS at a hospital involved in the project 
• Legally competent person 
• Pregnant with one child 
• Due date determined by ultrasound before 15 weeks of gestation
 **Exclusion criteria**• Multiple pregnancy 
• Needs an interpreter to communicate in Danish 
• Diabetes, both before and in pregnancy 
• Where there is a risk that delivery will take place prior to 39+5 weeks

**7. Data processing and analyses** 
Data collected from the two groups are used in a comparative analysis to identify any inter-group differences on the specified parameters. 
Statistical variables will be calculated according to the intention-to-treat principle and per-protocol using the analytical software program STATA. The primary endpoint will be analysed with a 5% significance level. The budget foresees the need for a statistician to assist with the data analyses.

**8. Ethics** 
The study was approved by the Scientific Ethics Committee of the Central Denmark Region. 
In addition, the study had been adapted to the trial guidelines for Good Clinical Practice. 
The project has been reported to clinicaltrials.gov (ClinicalTrials.gov Identifier: NCT00835003).

**8.1 Side effects, risks, complications or discomforts from participation**
As mentioned above, several centres perform ECS around 1 week before the date of expected confinement, but the gestational age may vary by several days, e.g. if the centre only perform caesarean sections on a particular day of the week. Therefore, the potentially assigned dates of delivery are in many cases the same as if the women were not included in the project. 
ECS at an early date may potentially cause more respiratory complications in the neonate, whereas ECS at a late date may slightly augment the risk of having an emergency caesarean section, which result in more complications in the mother. Rather few of the project procedures will be scheduled at the extreme ends of group dates. With regard to the woman, she will have an operation that was already decided for. All issues related to the surgery and post-operative treatment will remain unchanged. 
The results of the project are expected to outweigh any minimally increased risk of complications on the part of the individual project participant.

New knowledge on the health of pregnant women and neonates that may result from the project will benefit future women and neonates delivered by ECS.

**9. Funding** 
The project has received external funding from private and public funds. As of 1st Sept. 2010, the following grants had been received:
The Danish Research Council of Health and Illness 1,620,000 DKK (including overhead DKK 400,000), The Central Jutland Region’s Medical Research Foundation DKK 1,500,000 (including overhead 45,000 million), Aase and Ejnar Danielsen Foundation 200,000 (including overhead 6,000), Sophus Jacobsen and Wife Astrid Jacobsen's Foundation DKK 100,000 (including overhead 3,000) and Maria Dorthea and Holger From, Haderslev Foundation DKK 20,000 (including overhead 600).

**10 Research plan** 
1 June 2008 - 1 January 2009: Information meetings, official approvals obtained and application for funding, preparing materials and website.

1 March 2009 - 30 august 2011: Inclusion of pregnant women. Participation in postgraduate courses. Ongoing data entry. 
1 Sept. 2011 - 1 November 2011: Data collection completed, last data entered. 
1 Dec. 2011 - 31 Dec. 2012: Data analysis and compilation of articles and PhD thesis.

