**3.1 Null hypotheses**

1. That there is no difference in neonatal morbidity measured as the incidence of NICU admission, infection and respiratory morbidity.
2. That there is no difference in infant morbidity (health care utilization) within the first two months and the first two years of life.
3. That there is similar maternal perioperative and postoperative morbidity between the two groups.
4. That women's satisfaction with timing of the ECS do not differ between the two groups.
5. That there is no difference in the incidence of maternal depression between the two groups.

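### The section 10 calendar closes data collection on 1 November 2011 and analysis at the end of 2012, but the two-year child outcome needs follow-up to about 27 August 2013

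*Protocol*

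**What the plan says.** Null hypothesis 2 (section 3.1) reads "That there is no difference in infant morbidity (health care utilization) within the first two months and the first two years of life". Secondary outcome 4 (section 4.1) is "Outpatient treatment or control, or admission to a neonatal unit or paediatric ward within 2 months or 2 years after birth". Section 4.4 says that the two-month and two-year child data "are retrieved either from medical records on the data registration form or are extracted from" the national patient register, using personal identification numbers.

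The calendar is set in two places. Section 6 states "From January 2011, the study only includes women with a due date earlier than 30 August 2011". Section 10 gives "1 March 2009 - 30 august 2011: Inclusion of pregnant women", then "1 Sept. 2011 - 1 November 2011: Data collection completed, last data entered", then analysis and writing from 1 December 2011 to 31 December 2012. It lists no later step for two-year follow-up or for a later register extraction.

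**The concern.** The protocol sets a two-year horizon in its hypotheses and outcomes, and also a calendar that stops well before that horizon for many of the children. Both are stated rules, so this is a contradiction within the protocol and not a detail left to an analysis plan.

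If section 10 is followed literally, observed time for the two-year outcome ranges from about two months for the last births to the full two years for the earliest. A count of contacts within two years would then depend on date of birth as well as on health, and the two-year part of null hypothesis 2 could not be tested as defined.

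**Working it through.** **Inputs.** Latest due date 29 August 2011 (section 6: before 30 August). Pregnancy length: "with duration of pregnancy of 280 days" (section 4.2). Late-arm window up to 39+5 and target days 38+3 and 39+3 (section 4). Data close 1 November 2011 and end of analysis 31 December 2012 (section 10). Planned enrolment about 1,270 (section 5). Feasible inclusion 600 women a year from 1 March 2009 (section 6).

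**Last planned births.** Birth date = due date − (280 − gestational age in days).

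| Gestational age | Days | Last birth | Two months | Two years |
|---|---|---|---|---|
| 38+3 | 269 | 18 Aug 2011 | 18 Oct 2011 | 18 Aug 2013 |
| 39+3 | 276 | 25 Aug 2011 | 25 Oct 2011 | 25 Aug 2013 |
| 39+5 | 278 | 27 Aug 2011 | 27 Oct 2011 | 27 Aug 2013 |

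The stated close fits the two-month outcome, with 5 days to spare for the last births. It does not fit the two-year outcome. From 1 November 2011 to 27 August 2013 is 665 days, about 22 months. From 31 December 2012 to the same date is 239 days, about 8 months.

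**Share with two full years at a cut-off.** Only children born at least two years before the cut-off count: by 1 November 2009 for the data close, and by 31 December 2010 for the end of analysis. The protocol gives no distribution of birth dates, so two assumptions are used.

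*Even births* from 1 March 2009 plus a lag L (inclusion to first births) up to 27 August 2011, a span of 909 − L days. There are 245 days from 1 March 2009 to 1 November 2009, and 670 days to 31 December 2010.

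- Data close, L = 0: 245/909 = 27.0%, about 342 of 1,270.
- Data close, L = 61 days (2 months): 184/848 = 21.7%, about 275.
- Data close, L = 122 days (4 months): 123/787 = 15.6%, about 198.
- End of analysis, L = 0: 670/909 = 73.7%, about 936.
- End of analysis, L = 122 days: 548/787 = 69.6%, about 884.

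*600 births a year from 1 March 2009 with no lag*, the most favourable case tried.

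- Data close: 600 × 245/365.25 = 402, or 402/1,270 = 31.7%.
- End of analysis: 600 × 670/365.25 = 1,101, or 1,101/1,270 = 86.7%.

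**Result.** About 16–32% of children are two years old at data close, so about 68–84% are not (roughly 870 to 1,070 of 1,270). At the end of 2012, about 13–30% are still short (roughly 170 to 385).

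Even in the most favourable case, 1,270 births take 1,270/600 = 2.12 years, to about mid-April 2011. The last second birthdays then fall around mid-April 2013, after the plan has ended.

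**The case against.** The best counter-argument is that 1 November 2011 may close only the registration-form data. Section 4.4 describes form data as entered by a secretary and register data as extracted, and the date falls just after the last children reach two months. On that reading, section 10 is merely silent about the register. The reading is possible, but section 10 draws no such distinction, and the end of the whole plan still comes before the last second birthdays. The text between sections 10 and 12 was not in the copy at hand, so a step placed there would not have been seen.

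Several stronger readings might be inferred, and the protocol does not support them:

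- *The two-year data are lost.* They are not. Section 4.4 already allows register extraction, which can be run later without any visit.
- *Null hypothesis 2 as a whole is untestable.* Its two-month part fits the timetable.
- *The comparison is biased between arms.* Randomisation is concurrent and stratified by centre and previous caesarean, and target dates differ by 7 days. A common calendar cut-off gives the late arm only about a week less follow-up.
- *A truncated count would be published as a two-year result.* Nothing in the protocol says so.
- *The two data sources differ in completeness.* The protocol gives no evidence either way.

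**Conclusion.** The contradiction stands. Sections 3.1 and 4.1 require two years of follow-up for every child; section 10 ends data collection about 22 months, and the whole plan about 8 months, before the last child can have it.

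The dates follow from the protocol. The shares rest on the accrual assumptions shown. That most children are incomplete at data close holds under every pattern tried. The shortfall at the end of 2012 is less certain in size, but it is not zero under any of them.

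The importance is moderate. Only the two-year part of one secondary outcome and of one hypothesis is affected. The primary outcome, sample size, maternal outcomes and two-month outcomes are not. The cost of following the calendar is an incomplete outcome with unequal follow-up, rather than a material bias between the arms.

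**What to change.** Reconcile section 10 with sections 3.1, 4.1 and 4.4:

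- State that the late-2011 close applies to the primary, maternal and two-month outcomes.
- Add a separate, dated extraction from the national patient register after the end of August 2013, covering the children of all randomised women.
- Define the two-year outcome by a fixed two-year window from each child's birth, applied in the same way in both arms. This also removes the one-week difference that a common calendar cut-off would create.
- Say which items of outcome 4 come from the register. Section 4.1 lists details such as the physician and the type of treatment, and the protocol does not show that the register holds them.

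The cost is a revised timetable and one later extraction, with no extra participants or visits. The downside is that the two-year result is reported after the planned thesis period, and the protocol should say so.
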